##### Stage 2: selection of clusters

Survey clusters were defined as 5 km by 5 km land areas (25 km^2^), corresponding to the raster resolution of the modeled MR1 coverage from the 2019–2020 GDHS [33]. The primary sampling units (PSUs) are these clusters and includes all HDSS settlements within its boundaries. Clusters were selected within each district proportional to the district’s population size, ensuring that districts with larger populations contribute more clusters to the sample. Additionally, the selection process ensured that the combination of clusters were representative of both the population distribution and the overall MR1 coverage within each district.

For each cluster, let: ***a*** = the population size of the cluster; *b* = the cumulative population size of all clusters within a stratum (district); *c* = the predetermined number of individuals to be sampled from the cluster; and *d* = the total number of clusters to be sampled within the stratum (district).

The sampling interval (SI) per district is calculated as:$$\mathrm{SI}=\frac{b}{d}$$

To ensure randomness across districts, a random start (RS) between 1 and SI is chosen, and clusters are selected according to the arithmetic progression:$$n_{\mathrm{th}}\mathrm{value}=\mathrm{RS}+\left(n-1\right)\times \mathrm{SI}$$

using the cumulative population sizes to determine the sequence.

To adjust for potential sampling biases and to ensure that the sample is representative of the population, inverse probability weighting (IPW) was applied. The probability of selecting a cluster *(P*_*clust*_) and an individual within the cluster *(P*_*indiv*_) are computed as:

$P_{\mathrm{clust}}=\frac{a\times d}{b}$ and $P_{\mathrm{indiv}}=\frac{c}{a}$

Thus, the IPW for each individual is:$$\mathrm{IPW}=\frac{1}{P_{\mathrm{clust}}\times P_{\mathrm{indiv}}}$$

Clusters with fewer than 40 children aged 14 years or younger were excluded from the sampling frame to avoid selection bias and ensure statistical robustness. This threshold ensures that each selected cluster contributes sufficient data for meaningful analysis, particularly for the 1–4 years age group, which the study is powered by and is critical for assessing vaccine coverage and seroconversion following earlier MR1 and MR2 vaccination.

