##### Stage 3: selection of households

Within each selected cluster, a comprehensive list of households – defined according to the HDSS and spanning all settlements – will be extracted from the HDSS database. To ensure representativeness, this list will be randomized, and the first 40 households will be selected for inclusion. In clusters with fewer than 40 households across all the settlements, all households will be included. If the initially selected 40 households yield fewer than the expected number of eligible children, additional households from the randomly generated list will be sampled until the target is reached. Selected households will then be assigned to data collectors for field visits.

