##### Stage 4: selection of children

From the selected households, a list of all eligible children will be made. To ensure adequate power and based on the simulations conducted, 70 children per cluster will be sampled from these households according to the following age group allocation: < 1 year (10 children); 1–4 years (40 children); 5–9 years (10 children); 10–14 years (10 children).

This allocation (ratio 1:4:1:1) was chosen because the study was powered based on the 1–4 years age group, which is key to assessing vaccine coverage and immunity profiles following MR1 and MR2. In households containing multiple children within the same age cohort, one child per cohort will be randomly selected, ensuring that no more than one child from each age group is chosen from the same household. Sampling in each cluster will continue until 70 children are recruited, yielding a total sample size of 1,750 children from 25 selected clusters. To avoid selection bias, the survey Statistician and Data Manager, instead of field teams, will be responsible for the selection of households and generating random list of children to be recruited from each cluster.

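### In the smaller clusters that the frame admits, the cut-off, household and quota rules contradict each other, so 1,750 is a maximum and not a guaranteed sample size

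*Protocol article*

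**What the plan says.** Stage 2 of the Protocol article sets the size rule for the frame: "Clusters with fewer than 40 children aged 14 years or younger were excluded from the sampling frame to avoid selection bias". It then claims: "This threshold ensures that each selected cluster contributes sufficient data for meaningful analysis, particularly for the 1–4 years age group". The same section defines the probability of selecting an individual as c/a, with a the cluster's population size and c the number to be sampled from it.

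Stage 3 draws 40 households per cluster from a randomised list and adds: "In clusters with fewer than 40 households across all the settlements, all households will be included". If the yield of children is too low, "additional households from the randomly generated list will be sampled until the target is reached".

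Stage 4 allocates 10 children under 1 year, 40 aged 1–4, 10 aged 5–9 and 10 aged 10–14 to each cluster. It requires that "no more than one child from each age group is chosen from the same household", and concludes: "Sampling in each cluster will continue until 70 children are recruited, yielding a total sample size of 1,750 children from 25 selected clusters".

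Study setting and population puts the lower age limit at nine months. Descriptive analysis says that the weights will be adjusted to the numbers actually sampled per age group in each cluster.

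**The concern.** The eligibility rule counts 40 children of all ages, but the quota needs 70, of whom 40 must come from one four-year age band and from 40 different households. Stage 3 openly provides for clusters in which that many households do not exist. The only remedy is to add households, and it is exhausted once all of them are in. Sampling until 70 then has no end point.

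At stake are the stated total of 1,750, the 40 per cluster in the age group on which the study is powered, and the selection probabilities behind the weights. The youngest cohort adds a second constraint: it is labelled as under 1 year but covers only three months of age, so its quota of ten can be hard to fill in clusters well above the cut-off.

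**Working it through.** **1. The plan's own figure.** 10 + 40 + 10 + 10 = 70 per cluster, and 25 × 70 = 1,750. This reproduces, provided that every cluster fills every cohort.

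**2. Household limit.** With at most one child per cohort per household, a cluster of H households yields at most min(10,H) + min(40,H) + min(10,H) + min(10,H). For H from 10 to 39 this is 30 + H.

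| Households | Maximum aged 1–4 | Maximum in total |
|---|---|---|
| 20 | 20 | 50 |
| 30 | 30 | 60 |
| 39 | 39 | 69 |
| 40 | 40 | 70 |

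At H = 40 the quota is met only if every household has a child aged 1–4.

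**3. Child cut-off.** A cluster with 40 children is at least 70 − 40 = 30 short. It may be further short, because the cut-off also counts infants under nine months, who are not eligible.

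Number aged 1–4 among 40 children:
- From the Population projection counts, 25,608 + 8,111 = 33,719 are aged 1–4 among 43,428 + 13,858 = 57,286 aged 9 or under. Assume that the 10–14 group is as large as the 5–9 group (14,597 + 4,803 = 19,400). The share is 33,719 / 76,686 = 44%, or about 18 of 40.
- With equal numbers at each year of age (assumed), the share is 4/15 = 27%, or about 11 of 40.

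Forty children aged 1–4 therefore need about 91 children (40 / 0.44) to 150 children (40 × 15/4) aged 14 or under, before the household limit is applied.

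**4. Infant quota.** Study setting and population gives about 8,000 births a year in about 250,000 people. Ages 9–11 months are a quarter of a year: 8,000 / 4 = 2,000, or one per 125 residents. Ten need 10 × 125 = 1,250 residents at full participation, ignoring infant deaths and migration. The 220 + 149 = 369 villages average 250,000 / 369 = 678 people, so this is nearly two average villages (1,250 / 678 = 1.8). If the 3,223 + 944 = 4,167 children listed as 0–1 years are taken as one year of age, the figure rises to 10 × 250,000 / (4,167 / 4) = about 2,400 residents.

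**5. Effect on the total.** Each 40-child cluster removes at least 30: one gives at most 1,720, three at most 1,660. One cluster of 30 households gives at most 1,740.

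**6. Weights.** If a is a count of children, c/a = 70/40 = 1.75 at the cut-off and 70/69 = 1.01 at 69 children; it is above 1 throughout 40–69. In the weight, a cancels: IPW = 1 / [(a × d / b) × (c / a)] = b / (c × d). If a cluster of 40 is taken in full, the correct weight is b / (40 × d), but the formula gives b / (70 × d), too small by a factor of 1.75 unless it is adjusted.

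**The case against.** The strongest reply is that the conflict sits at an edge that the survey may never reach. Clusters are drawn by cumulative population. With the 76,686 children above, the average sampling interval is 76,686 / 25 = about 3,070, so a cell of 40–69 children has roughly a 1.3–2.2% chance of selection. That figure is approximate: district intervals are not given, and the later choice among simulated samples by power alters it. The 25 clusters are already drawn, and villages average 57,286 / 369 = 155 children aged 9 or under, so the quota for ages 1–4 may be met in all of them. This stands. A reader might infer that 1,750 cannot be reached, or that the rules clash in every cluster; the documents do not show that.

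A reader might also infer that a probability above 1 corrupts the analysis. It arises only if a counts children, which the text suggests but does not say. Because a cancels, it does no harm of its own, and the adjustment in Descriptive analysis can repair the weights. It cannot supply the missing children.

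On infants, Stage 3 lets sampling run past the first 40 households, populous cells are favoured, and fieldwork from April to August could bring new infants into range if lists were refreshed. So the infant quota is demanding, but not shown to fail.

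Two further inferences lack support. Nothing shows that the excluded small settlements are under-vaccinated. Nor does anything suggest that field teams would fill gaps with other ages, since Stage 4 gives selection to the statistician and data manager.

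Finally, a condensed article may leave contingency procedures to the full protocol. That would excuse silence, but here the rules as stated cannot all be followed in clusters that the text admits.

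**Conclusion.** The point holds for clusters with fewer than 40 households or fewer than 70 eligible children, and for these the text is wrong as written. The household result follows from the Stage 3 and Stage 4 rules alone, without any assumption. The cut-off of 40 children does not ensure enough children aged 1–4: it implies about 11–18 of the 40 required, depending on the assumed age structure. The infant quota reaches further up the size range, at about 1,250 residents per cluster, assuming evenly spread births and full participation.

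The figure of 1,750 is a maximum. The size of any actual shortfall is unknown, because the sizes of the 25 clusters are not in the text.

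Excluding small cells also does not avoid selection bias. It narrows the population to which the estimates apply, by an amount that the article does not give.

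**What to change.** Before fieldwork:

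- From the HDSS list, count the households with at least one eligible child of each cohort in each of the 25 selected clusters.
- Where a cohort cannot be filled under the one-per-household rule, take all eligible children of that cohort, allowing a second child per household with the weight reflecting it. Do not top up from other ages.
- Make the infant quota up to 10, and label the cohort as 9–11 months.
- Compute the individual selection probability by age group from the numbers actually sampled and eligible.
- Restate 1,750 as a maximum and give the achievable number beside it.
- Remove the claims that the 40-child cut-off secures enough children aged 1–4 and avoids selection bias. State that the excluded small cells lie outside the target population.

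Merging small cells or resetting eligibility is not advised at this stage. The clusters are drawn, so either step would change selection probabilities and could require a redraw, and merging would break the link between one cell and one modelled coverage value.

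The cost is a database query and revised wording. The stated total may become slightly smaller.

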Following cluster selection, a statistical power analysis was conducted. This analysis, based on detecting a 10% difference in protective immunity between different MR1 coverage levels and assuming an intraclass correlation coefficient (ICC) of 0.01 was conducted using simulations on a high-performance computing (HPC) system. The sampling procedure was simulated 10,000 times, and the final sample consists of the top 5% of simulations with the highest statistical power (see supplementary Table S1). Figure 3 shows the map of the 25 selected clusters from the BHDSS and FHDSS.

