### Statistical analysis and modeling

#### Descriptive analysis

We will use the R package *survey* to account for the complex sampling design when estimating age-specific and location-specific measles and rubella seroprevalence. Sampling weights will be applied to ensure representativeness, given the probability proportional to size sampling across the 25 randomly selected clusters. The weights will be computed based on the inverse probability of selection and will be adjusted to account for differences between the projected and actual population sampled per age group in each cluster.

Seroprevalence estimates will be generated for the four age cohorts (under 1 year, 1–4 years, 5–9 years, and 10–14 years) and across the sampled districts. We will report overall, HDSS level, district, ward, and age-specific seropositivity estimates. All 95% confidence intervals will be computed using linearized Taylor series variance estimation. We will use T-tests to assess the significance of differences in weighted seroprevalence between subgroups (e.g. age, sex, district). Associations between seropositivity and predictor variables (age, sex, geographic location) will be analyzed using univariate and multivariate generalized linear regression models, adjusting for the survey weights. Both unadjusted and adjusted odds ratios (ORs) with 95% confidence intervals will be reported.

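### The weights use the inclusion probability of an unrestricted PPS draw, although the clusters were also screened on MR1 coverage and on power

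*Protocol article*

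**What the plan says.** All references are to the protocol article.

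- **Draw (Stage 2: selection of clusters).** Clusters are 5 km cells taken by systematic sampling proportional to size within each district: "a random start (RS) between 1 and SI is chosen, and clusters are selected according to the arithmetic progression". The cluster probability is a×d/b and the child's probability within the cluster is c/a. The weight is the inverse of their product. Here a is the cluster's population, b the district total, c the number of children sampled per cluster and d the number of clusters in the district.
- **First restriction (same section).** Selection is said to have ensured that "the combination of clusters were representative of both the population distribution and the overall MR1 coverage within each district".
- **Second restriction (same section).** "The sampling procedure was simulated 10,000 times", and "the final sample consists of the top 5% of simulations with the highest statistical power". Power is "based on detecting a 10% difference in protective immunity between different MR1 coverage levels", "assuming an intraclass correlation coefficient (ICC) of 0.01". For results the reader is told to "see supplementary Table S1", which is not at hand.
- **Analysis (Descriptive analysis).** Sampling weights are applied "given the probability proportional to size sampling across the 25 randomly selected clusters". They are adjusted only for projected against actual population per age group in each cluster. Neither restriction on the cluster set is mentioned.

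**The concern.** A restricted draw is a legitimate design if the weights use the probabilities of that restricted design. Here the weights keep the probabilities of the unrestricted one. Both restrictions act through MR1 coverage, and vaccination is a main determinant of the outcome, seropositivity. If cells with particular coverage are retained more often than a×d/b implies, their children carry too much weight in the district and overall seroprevalence, which is the first primary objective. The Background puts the immunity needed to prevent measles outbreaks at 92–95%, a band 3 points wide, so an error of 1 to 2 points could change how an area is classified.

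**Working it through.** **1. The plan's own figure.** 10 + 40 + 10 + 10 = 70 children per cluster, and 25 × 70 = 1,750. This reproduces. The article prints no power value, alpha or base rate, so power cannot be reproduced.

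**2. What the weight contains.**
P_clust × P_indiv = (a×d/b) × (c/a) = c×d/b, so the weight is b/(c×d). Cluster size cancels. Before the age-group adjustment, every child in a district has the same weight, whatever the cell's coverage and however often the restrictions let that cell through.

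**3. What the inclusion probability becomes.** The top 5% of 10,000 draws is 500 draws. If the fielded set is one of these at random, a cell's inclusion probability is its frequency among the retained draws that also pass the coverage screen. This equals a×d/b only if passing is unrelated to which cells were drawn.

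**4. Does power depend on which cells are drawn?** Inputs from the article: 25 clusters, 40 children aged 1–4 years in each, ICC 0.01, a 10-point difference. Assumed: two-sided alpha 0.05, immunity 90% against 80%, normal approximation with pooled variance under the null.
- Design effect = 1 + 39 × 0.01 = 1.39. Effective n = 1,000/1.39 ≈ 719.
- Even split (about 360 per group): standard errors 0.0266 (null) and 0.0264 (alternative). z = (0.10 − 1.96 × 0.0266)/0.0264 ≈ 1.81, power 0.965.
- 20:80 split, smaller group at 90% (about 144 and 576): standard errors 0.0358 and 0.0301. z = (0.10 − 1.96 × 0.0358)/0.0301 ≈ 0.99, power 0.839. With the smaller group at 80%, power is 0.873.

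So ranking draws by power ranks them by coverage mix.

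**5. Simulated inclusion.** Assumed frames of 50, 75 and 100 cells in six districts, 25 clusters, 10,000 draws, cell coverage SD about 0.06. The power filter was applied without the coverage screen. The table gives realised inclusion divided by a×d/b.

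| Draws kept | Range of ratio |
|---|---|
| All 10,000 | 0.92 to 1.12 |
| Top 5%, power for a coverage gradient | 0.00 to 6.18 (up to 3 cells never kept) |
| Top 5%, power for low against high coverage | 0.17 to 1.66 |
| Top 5%, power differences pure simulation noise | 0.67 to 1.42 (sampling error around 1) |

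The formula holds without the filter. It fails when power depends on coverage.

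**6. From inclusion to bias.** If low-coverage cells hold a share q of children, are over-included by a factor k, and differ by 10 points in immunity, the bias is −10 × q × (k − 1) points. For example, q = 0.10 and k = 2 (both assumed) give −1.0 point. On assumed frames of about 102 cells, with 80% against 90% immunity:
- power filter alone: about 0.8 to 2.0 points with uneven coverage splits, and 0.2 to 1.4 with near-even splits;
- coverage screen first (best-matched tenth of draws or so, an assumed cutoff), then the power filter: 0 to 0.9 points in 17 of 18 uneven frames and 1.4 in the other, in several near zero or of opposite sign; 0.1 to 1.0 with near-even splits.

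In the frames of step 5, weighted mean coverage moved by less than 1 point.

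**The case against.** **The coverage screen is a safeguard.** Forcing the set to match district MR1 coverage works against over-inclusion of low-coverage cells. This stands. It brings the simulated bias mostly under 1 point, but it does not restore a×d/b, and it is itself a restriction that the weights ignore.

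**The main analysis is model-based.** The geospatial models may include routine coverage and population density as covariates. The protection is partial. Inclusion is optional, and the coverage covariate is at district level, so like the weight it cannot separate cells within a district. The weighted estimates remain in the plan.

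**The sequence is unclear.** The power paragraph places the power analysis after cluster selection and then lets it determine the final sample. Five hundred simulated sets are not one set of 25, and the article does not say how the fielded set arose. If power differences between draws were only simulation noise, a×d/b would hold approximately for the power filter. This limits what can be said about size. It does not reconcile the printed weight with the printed selection rule.

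**Stronger readings to avoid.** A reader might infer that seroprevalence is biased by a known amount, or downwards. Without the frame the documents support neither. A reader might also infer that the reported power is inflated. No power value is printed, and Table S1 is not shown. Power calculated exactly for the fielded clusters would be valid conditional on that set. In the simulation of a low- against high-coverage comparison, mean power was 0.96 over all draws and 0.965 in the top 5%.

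**Conclusion.** The point holds as an inconsistency between the printed selection rule and the printed weight. Cluster selection was restricted through MR1 coverage twice, while the weights assume no restriction and are constant within a district before the age adjustment. The design-weighted seroprevalence is therefore not guaranteed unbiased. Direction and size are unknown. On assumed frames the bias ranges from near zero to about 2 points, mostly under 1 point when the coverage screen is included. These figures rest on assumed cell counts, coverage distributions, immunity of 80% against 90%, and an assumed screening cutoff. The algebra in step 2 rests on none of them.

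**What to change.** 1. Re-run the stored selection code with both restrictions. For each cell, compute its inclusion frequency among the retained draws, with enough draws for stable values. Use this as P_clust in place of a×d/b. List cells with a frequency near zero as not covered, since no weight can recover them.
2. State how the fielded 25 clusters were taken from the retained sets. Step 1 is valid if they were drawn at random. If they were hand-picked or were the single best set, describe cluster choice as purposive and base seroprevalence on models that condition on cell-level MR1 coverage and population size.
3. Quote any power for the design as the median over all 10,000 draws. Label power for the fielded set as conditional on that set.

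The cost is a re-run of existing code and a changed weight formula, with no change in the field. The weights become somewhat more variable, and the quoted power may be lower.

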**Figure 3. f0003:**
[figure not shown]
The distribution of randomly selected serosurvey clusters across the (A) four districts in the Basse HDSS area and (B) two districts in the Farafenni HDSS area. Note: The green, yellow, and red tiles represent MCV1 coverage data at a 5 km by 5 km resolution based on The Gambia DHS (2019–2020) [33]. Blue dots indicate settlements/villages within the Basse and Farafenni HDSS sites, and red squares indicate the 25 selected 5 km by 5 km clusters.

